### Recruitment

Recruitment began on October 2, 2023, at 4 sites: the Universities of Windsor and Guelph in Canada and the Universities of Michigan and Nebraska-Lincoln in the United States. In year 2 of the trial, recruitment was ended at the University of Nebraska and paused at the University of Michigan due to the departure of the site principal investigators (PIs) from those institutions. In year 3 of the trial, recruitment is planned at the University of Guelph, the University of Michigan, the University of Maryland, and the University of Central Florida. The 6 total sites represent diverse students, sizes, and contexts (eg, rural vs urban, proportion of students in residence, racial, and geographic diversity). Recruitment will only take place during the academic year when classes are in session. Multiple methods are used to attract participants to the study, including (1) recruitment emails through the registrar, faculties, or departments to all eligible students, (2) research participant pools, (3) social media ads or posts to relevant Facebook groups (eg, groups for students at a particular university), and (4) flyers will be distributed at on-campus events, posted in women’s bathrooms on campus, and sent digitally to student newsletters/newspapers, student organizations, or student-specific listserves at the sites of Universities. Not all recruitment methods will be used at all sites (eg, emails are permitted through the Registrar at certain sites but not others).

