### Randomization

When participants have completed their screening interview, they receive an email inviting them to complete the baseline survey (see section below on assessments for more details). The baseline survey must be completed no less than 24 hours before their first program session (or only program session for control participants). The email contains an individualized URL taking them directly to this first survey, which takes 30-45 minutes.

Randomization of the pair will occur once both participants in the pair complete their screening interview and baseline survey, and no later than 24 hours before the first (or only) session. If one member of the pair fails to complete the baseline survey, the other member of the pair will be given the choice of continuing in the study with a different partner (time permitting), rescheduling for a later intervention session, or discontinuing the research. In rare circumstances, that is, if the participant has been re-paired once or more, there is insufficient time to re-pair, or no one else is available for a new pairing, she will be individually randomized and permitted to complete the intervention by herself. Once the pair is randomized, they are sent a Zoom link for the session through REDCap. This link does not identify their random assignment. The facilitators/research assistant (RA) reveal the assignment once everyone is present in the Zoom room at the scheduled time.

The trial biostatistician is responsible for setting up the randomization protocols in REDCap. Randomization is stratified by site using permuted block sizes of 2 and 4, and participant pairs are randomized 1:1 to the IDEA^3^ program or control. Randomization occurs after baseline completion so that participation in the trial cannot be affected by knowledge of intervention assignment. The site coordinators generating the random assignment for a participant pair are not able to view the random allocation sequence.

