### Sample Size Considerations

In calculating the sample size for the proposed trial, we used estimates of the 1-year incidences and difference in completed rape from the previous trial (9.8% control vs 5.2% EAAA=4.6% difference [5]). However, we conservatively powered the trial so we can still detect meaningful differences even if IDEA^3^ is less efficacious than in-person EAAA, that is, it achieves 80% of the previously observed difference (80% of 4.6%=3.7%). Therefore, assuming 1-year incidences of completed rape in the proposed trial of 9.8% in the control group versus 6.1% in the intervention group, a sample size of 1676 will have 80% power to detect an absolute difference of 3.7% (relative risk reduction of 37.75%) at a 2-sided 5% level of significance. As participants in the IDEA^3^ sessions will be in pairs, the sample size is further inflated by a design effect of 1.031, based on a within-pair correlation of 0.031 from the previous trial. Including an estimated maximum 10% lost-to-follow-up, a total of 1920 participants will be enrolled in the trial (1920=1676×1.031/0.90). Using estimates for the secondary outcomes from the previous trial [5] and similarly, assuming 80% efficacy compared with the in-person intervention, the proposed sample size yields 97% power for comparing 1-year differences in attempted rape (9.3% vs 4.6%), 92% power for sexual coercion (22.6% vs 16.1%), and 99% power for sexual contact (39.1% vs 28.5%). Using estimates for the tertiary outcomes from the previous trial [21] and similarly, assuming 80% less efficacy, the proposed sample size yields > 99% power for comparing 1-week postintervention group differences in risk perception (Cohen *d* 0.58), rape myths (Cohen *d*=0.48), risk detection (Cohen *d*=0.54), and self-defense self-efficacy (Cohen *d*=0.64).

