### Statistical Analyses

Analyses will be performed after all participants have completed their 1-year follow-up survey. Following a modified intention-to-treat principle, a participant will be included in the analyses if they are randomized and complete one or more postrandomization surveys. The analyses will compare the incidence (ie, first occurrence) of each primary and secondary outcome between the IDEA^3^ and control groups with Kaplan-Meier failure curves (indicating the cumulative percentage of first outcomes among women in the respective groups) and log-rank tests. Participants who are lost to follow-up or drop out will have their data censored at the time of last contact. To account for the correlation between the paired observations, variance estimates will be appropriately inflated for within-pair clustering with the use of estimates of the design effect [50]. In case of baseline imbalances in participant characteristics, Cox proportional hazards regression models with a robust sandwich covariance matrix to account for the clustering will be used to compare the IDEA^3^ and control groups while controlling for the confounding factors. The literature [24,51,52] suggests that prior SA can be a modifier with respect to the effectiveness of SA resistance interventions. Therefore, intervention effects will be compared for women with and without SA histories at baseline by adding a cross-product term to the Cox regression model and testing for statistical significance. For the tertiary outcomes, which are all continuous, linear mixed models will be used to analyze the data that mirror a multilevel repeated-measures study design. A random intercept will be included in the models to account for the correlation between the paired observations, and a first-order autoregressive covariance structure will be used to characterize the interdependence of the repeated measures over time. A cross-product term between group and time will also be included in the models. Participants who are lost to follow-up or drop out can affect the validity of the group comparison if (1) the outcome is related to being lost or dropped, and (2) it is differential between groups. Therefore, baseline characteristics of women who are lost and drop out will be compared with women who complete the trial. In addition, the missing data mechanism will be formally tested [53] to determine whether it is Missing Completely at Random or missing at random. For completeness in assessing the effect of missingness, 2 additional analyses will be conducted: (1) a “per-protocol” analysis among participants who attend all sessions and respond to the 1-year SES-SFV questions; (2) multiple imputation of 5 data sets using a discriminant function for binary outcomes and Markov chain Monte Carlo for continuous outcomes, assuming the missing data mechanism is missing at random.

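### Randomization is stratified by site, but the described analyses account for pairing only and never name site: a minor gap with a wording-only fix

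*Protocol article*

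**What the plan says.** The protocol article's Randomization section states: "Randomization is stratified by site using permuted block sizes of 2 and 4, and participant pairs are randomized 1:1". Under Recruitment it describes the sites as differing: "The 6 total sites represent diverse students, sizes, and contexts".

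For the primary and secondary outcomes, the Statistical Analyses section names "Kaplan-Meier failure curves (indicating the cumulative percentage of first outcomes among women in the respective groups) and log-rank tests". The design feature it carries into these tests is the pair: "variance estimates will be appropriately inflated for within-pair clustering with the use of estimates of the design effect". Regression adjustment is conditional: "In case of baseline imbalances in participant characteristics, Cox proportional hazards regression models with a robust sandwich covariance matrix" are to be used, controlling for the confounding factors. A Cox model also serves to test the interaction with prior sexual assault. The mixed models for the tertiary outcomes have a random intercept for the pair, an autoregressive structure over time and a group-by-time term.

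Site appears in none of these analyses. The article does not call the log-rank test unstratified; it is silent.

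**The concern.** When allocation is blocked within site, differences between sites are largely removed from the true sampling variation of the treatment comparison. An analysis that leaves site out still counts those differences as noise. Its variance estimate is then too large for the design, and the test is somewhat conservative.

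The Statistical Analyses section is otherwise specific. It gives the covariance estimator, the cross-product terms, the repeated-measures structure and the number of imputations, and it says how pairing enters. The other feature of the randomization, the site stratum, drops out. The covariate rule does not fill the gap. It responds to imbalance in participant characteristics; site is not clearly one of these, and small blocks within site keep it close to balanced.

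At stake is a little precision in a trial planned at exactly 80% power. It also matters that the form of the primary test is fixed before outcomes are analyzed in an open-label study.

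**Working it through.** **1. The plan's own figure.** Inputs from Sample Size Considerations: "9.8% in the control group versus 6.1% in the intervention group", two-sided 5%, power 80%, design effect 1.031, loss 10%.

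Two-proportion formula with pooled variance under the null and no continuity correction, mean incidence (0.098 + 0.061)/2 = 0.0795:

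- 1.960 × √(2 × 0.0795 × 0.9205) = 0.7498
- 0.8416 × √(0.098 × 0.902 + 0.061 × 0.939) = 0.3212
- n per arm = (0.7498 + 0.3212)² / 0.037² = 837.9, so 838, or 1676 in total
- 1676 × 1.031 / 0.90 = 1919.95, so 1920

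The stated sizes reproduce. Site does not enter them, so stratifying the analysis leaves them unchanged.

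**2. Simulated effect of leaving site out.** The hazard ratio implied by the planning rates is ln(0.939)/ln(0.902) = 0.610. The evaluable number is 1920 × 0.90 = 1728. The article gives no site rates or site sizes, so these are assumptions: six sites of 400, 400, 350, 150, 214 and 214 women, with control incidences averaging 9.8%. Pairs were allocated in blocks of 2 and 4 within site, event times were exponential and censored at one year, and the log-rank variance was inflated by 1.031. Both tests were applied to the same 4000 simulated trials per scenario.

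| Control incidence across sites | Power without site | Power stratified | Type I error without site | Type I error stratified |
|---|---|---|---|---|
| Equal, 9.8% | 80.4% | 80.4% | 5.1% | 5.1% |
| 2-fold, 7.1% to 14.2% | 80.0% | 80.2% | 4.7% | 4.7% |
| 4-fold, 4.3% to 17.0% | 80.3% | 80.7% | 5.2% | 5.2% |
| 10-fold, 2.3% to 23.0% | 79.3% | 80.7% | 4.2% | 4.8% |

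Before rounding, the 4-fold row is 80.25% against 80.73%, a gap just under half a point. The simulation error of a single entry is √(0.8 × 0.2/4000) = 0.6 points for power and √(0.05 × 0.95/4000) = 0.35 points for type I error.

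**3. Cross-check by variance share.** Between-site variance divided by p(1 − p), for two assumed sets of six equally sized sites:

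- 5, 7, 8, 8, 9, 11%: 0.000333/0.0736 = 0.0045
- 4, 6, 8, 9, 10, 12%: 0.000681/0.0750 = 0.0091

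Site would explain about 0.5% to 0.9% of the outcome variance, which agrees with the small differences in the table.

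**4. A limit of the simulation.** It fixed the design effect at 1.031. If the design effect is instead estimated from this trial's data without site, the within-pair correlation absorbs site variance, because both members of a pair attend the same university. Scale the total variance to 1 = site + pair + error. The estimate is then 1 + pair + site, while the true value under blocking is 2 × pair + error. The difference is 2 × site. With the shares above this is about 0.9% to 1.8%. For the larger, the critical value in true standard errors is 1.960 × √1.018 = 1.978, and power is Φ(2.802 − 1.978) = 79.5% instead of 80%. The direction is again conservative. For wider site spreads the cost would exceed the figures in the table.

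**The case against.** The strongest objection is that this is a condensed journal article. Whether a log-rank test carries the randomization strata is a detail often left to a statistical analysis plan, and a site-stratified test is compatible with the text. That stands in part: the point cannot be put as a contradiction or as proof that the final analysis will ignore site. What remains is that the section spells out how pairing and covariates enter, and the rule it gives would probably leave site out.

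A second objection is that the effect is close to nil for plausible site differences. That stands, and it makes the point minor.

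A reader might infer more, and the documents do not support it:

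- **An inflated false-positive rate.** The simulations show none; at the extreme spread the test without site is slightly conservative.
- **A hazard ratio pulled materially toward 1.** With a true within-site value of 0.610 and the two sets of assumed incidences in step 3, the pooled value is about 0.611. With an assumed range of 2% to 20% it is still only 0.615 to 0.616.
- **Follow-up that differs by site because sites opened and closed in different years.** Recruitment reports that "recruitment was ended at the University of Nebraska and paused at the University of Michigan". But surveys are timed from each participant's own baseline, and analysis waits until everyone has completed the one-year survey. Staggered recruitment does not by itself shorten anyone's follow-up.
- **Site can never be imbalanced.** Blocking balances the randomized pairs. The analysis set omits women with no postrandomization survey, so exact balance is not guaranteed there.
- **Every site will have ample pairs.** The article gives no site counts.

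**Conclusion.** The point holds as a minor mismatch between how the trial randomizes and how the article says it will analyze. Leaving site out does not threaten validity: type I error is not inflated, and the test is at most slightly conservative. The power cost is between zero and just under half a point for up to a 4-fold spread in site incidence, and about 1.4 points for a 10-fold spread. These figures rest on assumed site rates and site sizes, on a common hazard ratio across sites, and on a design effect held at 1.031. The required sample size stays at 1676, inflated to 1920. The case for acting is that the change aligns the variance with the design at no cost, not that much power is at risk.

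**What to change.** State in the analysis section, or confirm in the statistical analysis plan, that:

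- the primary and secondary log-rank tests are stratified by site, with the pair-level variance correction kept and any design effect estimated within site;
- all Cox models, including the one for the prior-assault interaction, are stratified by site with a covariance robust to pair clustering;
- the mixed models for the tertiary outcomes include site as a fixed effect.

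If site is left out on purpose, say so and give the reason. The cost is wording only: no change to sample size, randomization, data collection or trial procedures. Data collection runs to May 2027 according to the Results section, so this can be settled well before the analysis.

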#### Intervention Condition

The IDEA^3^ SA resistance program follows the same structure as EAAA, with four 3-hour units led by 2 near peer-facilitators with content designed to help women more quickly and effectively recognize and resist coercion (see the *Introduction* section for more detail). IDEA^3^ retains the interactive modality of EAAA by using games, discussions, and other activities.

This intervention is presented by a pair of highly trained woman-identified “near-peer” program facilitators (ie, a few years older than the participants). Unlike the original in-person intervention, a tech facilitator is present at all sessions to facilitate the Zoom technology, troubleshoot participant technical difficulties, assign breakout rooms, provide participants with links to external games/group apps, record sessions, and perform other technical duties before, during, and after each session. The presence of the tech facilitator allows the program facilitators to focus on content delivery and facilitating participant discussion and engagement.

Participants receive the intervention in pairs via Zoom in a private room with enough floor space to practice basic self-defense techniques, and where they know they will not be disturbed. If a pair of participants does not have an appropriate room available to them, a university-sponsored space for each pair is arranged. These Zoom sessions include a minimum of 1 and a maximum of 8 pairs of participants (16 women total) taking part in the intervention together.

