#### Control Condition

Participant pairs assigned to the “usual care” control arm will receive one 60-minute session. The workshop focuses on (1) defining consent, including what components need to be present for consent to be meaningful, and (2) expanding the ways in which participants feel comfortable giving, refusing, and asking for consent. The control condition was selected to mimic what is currently available, “usual care” on typical college campuses, which is a brief consent workshop. The content is therefore based on the common components of consent workshops held at the study sites and community-based consent workshops (confirmed with participating campus materials and in consultation with the Ontario Coalition of Rape Crisis Centres).

As with the intervention arm condition, participants receive the consent workshop in pairs via Zoom in a private room (their own or provided to them on campus). These Zoom sessions include up to 8 pairs of participants (16 max) taking part in the workshop together. The control workshop is given by a well-trained RA. Participants who are assigned to the control arm will be informed of the importance of the control group to the study and their ongoing participation. They are made aware that they will be contacted in a year and offered the opportunity to take the full IDEA^3^ program.

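### The sample size and analyses allow for correlation within pairs only; if shared live sessions add any correlation between pairs after randomisation, standard errors are too small and power falls below 80%

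*Protocol article*

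**What the plan says.** Pairs are randomised 1:1, stratified by site (protocol article, Randomization). Both programs are then delivered to several pairs at once.

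- Intervention Condition: "These Zoom sessions include a minimum of 1 and a maximum of 8 pairs of participants (16 women total"), over four 3-hour units with two shared program facilitators.
- Control Condition: "These Zoom sessions include up to 8 pairs of participants (16 max) taking part in the workshop together", for one 60-minute workshop.

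Sample Size Considerations assumes "9.8% in the control group versus 6.1% in the intervention group" and says that "a sample size of 1676 will have 80% power to detect an absolute difference of 3.7" percentage points, "at a 2-sided 5% level of significance". It then states that "the sample size is further inflated by a design effect of 1.031, based on a within-pair correlation of 0.031 from the previous trial". After a 10% allowance for loss to follow-up, the total is 1920.

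Statistical Analyses stays at the same level. For the log-rank comparisons, "variance estimates will be appropriately inflated for within-pair clustering with the use of estimates of the design effect". The mixed models for the tertiary outcomes have a random intercept for paired observations. The Cox model, used if there is baseline imbalance, has a robust sandwich variance for clustering. The cluster is not named there, but the pair is the only one the section defines. No session or facilitator term appears anywhere.

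**The concern.** Pairs sit wholly inside session groups. The Introduction presents learning from peers and facilitators as a key advantage of the synchronous group format. Women in the same IDEA3 group share facilitators, discussions and, if they choose, a group chat. The plan accepts that two paired women have correlated outcomes, but implicitly sets the correlation between different pairs in one session to zero, without a reason.

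If that correlation is positive, the pair-only variance omits a component that the way of treating women creates. Standard errors for primary, secondary and tertiary outcomes would be too small, the primary test would reject somewhat more often than 5%, and 1920 women would give less than 80% power. This is not detail left for an analysis plan: the article names the clustering level and puts a figure on it.

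**Working it through.** **Inputs.** From Sample Size Considerations: incidences 0.098 and 0.061, two-sided alpha 0.05, power 80%, pair correlation 0.031, and this on loss: "Including an estimated maximum 10% lost-to-follow-up". From the two condition sections: at most 16 women per session. Not in the documents, so assumed: the correlation ρ between women in the same session but different pairs (0.005, 0.01, 0.02), and the typical session size m (8 or 16).

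**Step 1: reproduce the plan.** The two-proportion formula with pooled variance under the null and no continuity correction gives 837.9, so 838 per arm, or 1676. Pair design effect: 1 + (2 − 1) × 0.031 = 1.031. Total: 1676 × 1.031 / 0.90 = 1919.95, so 1920. Both figures reproduce. Evaluable women: 1920 × 0.90 = 1728, or 864 per arm. Effective size: 864 / 1.031 = 838 per arm, giving 80.0% power. There is no slack.

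**Step 2: add the session level.** Each woman has one partner (correlation 0.031) and m − 2 other women in her session (correlation ρ):

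DE = 1 + 0.031 + (m − 2) × ρ

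- m = 16: DE = 1.101, 1.171, 1.311 for ρ = 0.005, 0.01, 0.02.
- m = 8: DE = 1.061, 1.091, 1.151.

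**Step 3: power.** Use the same two-proportion test with effective sizes. With clustering in the IDEA3 arm only, control has 864 / 1.031 = 838 and IDEA3 has 864 / DE (at m = 16: 785, 738, 659). With both arms clustered, each has 864 / DE.

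**Step 4: type I error of the pair-only test.** With both arms clustered:

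α = 2 × [1 − Φ(1.96 × √(1.031 / DE))]

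With the IDEA3 arm only, DE is replaced by the mean of 1.031 and DE, because the arms have equal size and equal outcome variance under the null. Example at m = 16, ρ = 0.01: mean = (1.031 + 1.171) / 2 = 1.101; 1.96 × √(1.031 / 1.101) = 1.897; α ≈ 5.8%.

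| Case | Quantity | ρ = 0.005 | ρ = 0.01 | ρ = 0.02 |
|---|---|---|---|---|
| IDEA3 arm only, m = 16 | Power | 78.6% | 77.1% | 74.3% |
| | Type I error | 5.4% | 5.8% | 6.6% |
| IDEA3 arm only, m = 8 | Power | 79.4% | 78.8% | 77.5% |
| | Type I error | 5.2% | 5.3% | 5.7% |
| Both arms, m = 16 (upper bound) | Power | 77.4% | 74.8% | 70.0% |
| | Type I error | 5.8% | 6.6% | 8.2% |

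At ρ = 0 every case returns 80.0% and 5%.

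**The case against.** A reader might infer that the intervals are certainly too narrow, or that a type I error near 8% is to be expected. The documents support neither, for five reasons.

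1. **No session correlation and no mean session size is given.** If pairs in a session are uncorrelated, the pair-level variance is right. Sixteen is a ceiling, and a session may hold a single pair.
2. **Sessions are not randomised to arms; pairs are.** Women state their availability for a schedule block before randomisation, whichever arm they will enter, and randomisation is stratified by site. Correlation from site, term or block is therefore largely common to both arms and cancels in the comparison. The type I figures need session effects that arise after randomisation, vary between sessions and average to zero across arms.
3. **The arms differ in contact.** Twelve hours of group work applies to IDEA3 only. One 60-minute workshop may induce little correlation, so equal clustering in both arms is a bound and not the natural case.
4. **The range for ρ is limited.** Pair members share a session, so 0.031 should already contain any session component, if pairs in the previous trial also shared sessions. A ρ of 0.02 would make about two thirds of it a session effect (0.02 / 0.031 = 0.65). Manuals, common training and fidelity checks on 25% of recordings also aim to limit variation between sessions.
5. **Stated power for the other outcomes is high** (97%, 92% and 99% for secondary outcomes, above 99% for the tertiary outcomes listed), so modest inflation does little harm there.

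All five stand, and they reduce the size of the problem. They do not remove it: the session level is absent from both the calculation and the analyses, and peer and facilitator effects after randomisation are part of how the program is meant to work.

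**Conclusion.** The omission is certain; its consequence is conditional. Any positive between-pair session correlation arising after randomisation makes pair-only standard errors too small and puts primary-outcome power below 80%. In the more plausible case, with clustering mainly in the IDEA3 arm, the loss runs from under 1 percentage point (8 per session, ρ = 0.005) to about 6 points (16 per session, ρ = 0.02), with type I error of about 5.2% to 6.6%. The bound with both arms equally clustered in full sessions reaches 70.0% power and 8.2%. These figures rest on assumed values of ρ and m. For secondary and tertiary outcomes the issue is the standard errors, not the stated power. The plan should be changed, because the remedy is cheap; the arithmetic behind 1676 and 1920 is correct and the trial size need not change.

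**What to change.** **Statistical Analyses.** Base the log-rank variance and the Cox robust sandwich on the assigned session group, with pairs nested within it and no-shows kept in the group for which they were scheduled. In the mixed models, add a session-group random intercept above the pair intercept and let it differ by arm.

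**Sample Size Considerations.** Keep 1920. Restate power as a range over an assumed session correlation, and include the case with clustering in the IDEA3 arm only.

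**Cost.** The session identifier must be kept for each randomised woman. Attendance at assigned sessions is recorded, so it should be available, though the article does not say so outright. Full sessions would give 1920 / 16 = 120 groups, and smaller sessions more, which is enough for a sandwich estimator. Intervals may be slightly wider, and the stated power becomes slightly less favourable. The change can still be prespecified: 683 women had been enrolled by August 2025, and analysis waits until all 1-year follow-up is complete.

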#### Baseline Survey

After completing the screening interview and giving consent, participants are invited to complete the baseline survey. The survey includes a number of demographic questions (eg, year of study, age, ethnicity, sex assigned at birth, gender identity, sexual identity, sexual orientation, current relationship status, number of sexual partners, and age of first sexual contact), primary outcome assessment (Sexual Experiences Survey-Short Form Victimization [SES-SFV]) [28], secondary outcomes scheduled for the baseline (Self-defense Self-efficacy Scale) [29], perceived risk for acquaintance SA [30] (1 item), the Perceived Causes of Rape Scale [31], and the Updated Illinois Rape Myth Acceptance Scale [32], and tertiary outcomes (Acceptance of Sexualized Aggression Scale [33], 13 items from the Sexual and Reproductive Empowerment Scale [34]).

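### The covariate-adjusted comparison is run only if baseline imbalance is seen and is not ranked against the unadjusted log-rank test; the covariates should be fixed in advance

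*Protocol article*

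**What the plan says.** The Statistical Analyses section of the Protocol article compares the first occurrence of each primary and secondary outcome by Kaplan-Meier curves and log-rank tests. Variance is inflated by a design effect for the pairing. This part is unconditional and names no covariates.

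A second comparison of the arms follows, under a condition: "In case of baseline imbalances in participant characteristics, Cox proportional hazards regression models with a robust sandwich covariance matrix" are to be used, controlling for factors described only as confounding. The section does not say whether this result replaces the log-rank result or stands beside it.

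Prior sexual assault (SA) has one fixed role. The section notes that "prior SA can be a modifier with respect to the effectiveness of SA resistance interventions" and plans an arm-by-history cross-product term in a Cox model. The history is available for everyone: the Baseline Survey section lists "primary outcome assessment (Sexual Experiences Survey-Short Form Victimization [SES-SFV" among the baseline measures, and the Randomization section places randomization after baseline completion. Randomization is stratified by site only.

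**The concern.** In a properly concealed randomized trial, a baseline difference between arms is a chance event. A covariate is worth adjusting for because it predicts the outcome, and that can be judged before any data are seen. Selecting covariates by observed imbalance selects on the arm difference instead. It can bring in a variable that hardly predicts the outcome and leave out one that does.

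The rule also leaves two possible results for the primary outcome, unranked, with the existence and content of the second depending on the arm-level baseline data. The two differ in more than covariates: the log-rank test handles pairs by a design-effect inflation, the Cox model by a sandwich variance. The trial has 80% power under its own assumptions, so a result near the significance boundary is plausible. There, a reader could not tell which analysis was meant to decide.

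Meanwhile the baseline variable that the plan itself singles out is absent from the default main comparison, and so is the only stratification factor.

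**Working it through.** **1. The plan's own sample size.** Inputs from Sample Size Considerations: "9.8% in the control group versus 6.1% in the intervention group", and "relative risk reduction of 37.75%) at a 2-sided 5% level of significance"; the claim is that "a sample size of 1676 will have 80% power to detect an absolute difference of 3.7"%. The two-proportion formula with pooled variance and no continuity correction gives 838 per arm, so 2 × 838 = 1676. The section then has this "inflated by a design effect of 1.031, based on a within-pair correlation of 0.031", and 10% loss: 1676 × 1.031 / 0.90 = 1919.95, i.e. 1920. Both figures reproduce. They assume an unadjusted comparison.

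**2. Implied hazard ratio and events.** HR = ln(1 − 0.061) / ln(1 − 0.098) = 0.610. Expected events: 838 × (0.098 + 0.061) = 133. Schoenfeld's formula needs 129 and Freedman's 134, so the log-rank test has about the stated power.

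**3. How often chance alone would pull the trigger.** Assume k independent characteristics, each called imbalanced at p < 0.05. The chance of at least one is 1 − 0.95^k:
- k = 5: 23%
- k = 10: 40%
- k = 15: 54%

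The threshold, k and independence are assumptions. The Baseline Survey section gives at least nine demographic items plus several scales.

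**4. Effect on error rate and power.** Simulation: 838 women per arm, exponential event times, control one-year risk 9.8%, arm HR 1 (12,000 runs per scenario) or 0.610 (3,000 runs). The unadjusted log-rank test is compared with one stratified by prior SA. Assumed, not in the document: prior-SA prevalence 25% or 50%; hazard ratio of prior SA for the outcome 1.5, 2, 3 or 4. Pairing is ignored. The trigger is a p < 0.05 imbalance in prior SA.

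| Strategy | Type I error | Power |
|---|---|---|
| Never adjust | 4.8-5.2% | 78.7-80.2% |
| Always adjust | 4.7-5.2% | 79.7-81.0% |
| Adjust if imbalanced, applied mechanically | 4.6-5.1% | 78.8-80.2% |
| Report the more favourable of the two | 5.1-6.0% | not a legitimate strategy |

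Monte Carlo standard error is √(0.05 × 0.95 / 12000) = 0.2 points for type I error and √(0.8 × 0.2 / 3000) = 0.7 points for each power figure. Strategies were compared on the same simulated trials, and the within-scenario gain from always adjusting was about 0 to 1.5 points.

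**5. Where the gain comes from.** The standard error of the log hazard ratio is set by the event counts: √(1/(838 × 0.098) + 1/(838 × 0.061)) = 0.178. A separate Cox simulation (1,500 runs per scenario, prior-SA prevalence 25%, 30% or 50%, hazard ratio 1.5, 2 or 4) gave about 0.179 both with and without prior SA in the model. Adjustment moved the log hazard ratio away from zero by at most about 0.01. The power gain therefore comes from a slightly larger conditional effect, not from a smaller standard error.

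**The case against.** The strongest reply is that nothing here is invalid. The log-rank test is planned unconditionally, a randomized unadjusted comparison is sound, and the trigger looks at baseline characteristics, not outcomes. This stands, and it rules out two stronger readings. A reader might infer that the primary test itself switches with the data; the text does not say that the Cox result takes over, only leaves it unranked. A reader might also infer that the rule breaks the 5% level. Applied mechanically to prior SA, it does not. Inflation needs someone to report the better of two results, and no sentence permits that. The mechanical case was, however, examined for one covariate only, not for a search across many.

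A second reply is that prior SA is not ignored. That is right: it enters the effect-modification model whatever the balance, and only the main comparison omits it. The word confounding may also imply that covariates would have to relate to the outcome. Even so, imbalance would still decide whether adjustment happens.

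A third reply is that the imbalance threshold and the covariate list are details for an analysis plan not shown here. Agreed, and their absence from the article is not part of this point. The conditional rule is stated in the article, and adding a threshold would not remove it.

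Last, a large gain in precision might be expected from adjusting for a strong risk factor. With about 133 events the standard error barely changes, so that expectation is not supported.

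**Conclusion.** The point holds in a limited form. The article fixes a poor rule: adjustment depends on observed imbalance, and the resulting Cox comparison is not ranked against the log-rank test. The cost is a data-dependent choice between two results and a small loss of power. Type I error is near 5% if the rule is applied mechanically to prior SA, and at most about 6% if the more favourable result could be reported. The power forgone is about 0 to 1.5 points. These sizes rest on the assumed prevalence and hazard ratio of prior SA, a p < 0.05 trigger on that one variable, and no allowance for pairing, which is minor at a design effect of 1.031.

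The sample size is unaffected. The issue is clarity and credibility of the primary result, of moderate to low severity, and worth correcting because it is cheap.

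**What to change.** Delete the imbalance trigger. Before outcome data are analysed, name one primary analysis with covariates fixed whatever the observed balance: baseline SA history from the SES-SFV, defined as in the effect-modification analysis, and site as the stratification factor. Either of these would serve:
- a Cox model with arm, SA history and site, and variance robust to pairing; or
- a log-rank test stratified by SA history and site, with the pairing allowed for.

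Label the unadjusted log-rank test as supportive, and keep the arm-by-history term as a separate modifier analysis. If the sponsor prefers to keep the unadjusted test as primary, saying so and prespecifying the adjusted model as a sensitivity analysis would also remove the ambiguity, at the price of the small power gain.

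The cost is a change to the analysis text. Both variables are already held for every randomized participant, and since analysis waits for all one-year follow-up, with data collection running to May 2027, there is time. Two drawbacks should be acknowledged. An adjusted hazard ratio is a conditional quantity that differs slightly from the unadjusted comparison behind 1676/1920, although those numbers need no change. Full stratification by six sites and SA history makes 12 strata, or about 133 / 12 = 11 expected events each on average; the Cox model with site as a covariate avoids splitting the data that finely.
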